## Abstract

**Background:**

Diabetes mellitus is one of the four priority non-communicable diseases worldwide. It can lead to serious long-term complications and produces significant costs. Due to the chronicle character of the disease, it requires continuous medical treatment and good therapy adherence of those suffering. Therefore, diabetes self-management education (DSME) (and support DSMES) plays a significant role to increase patient’s self-management capacity and improve diabetes therapy. Research indicates that these outcomes might be difficult to maintain. Consequently, effective strategies to preserve the positive effects of DSMES are needed. Preliminary results show that peer support, which means support from a person who has experiential knowledge of a specific behavior or stressor and similar characteristics as the target population, is associated with better outcomes in terms of HbA_1c_, cardiovascular disease risk factors or self-efficacy at a lower cost compared to standard therapy. Peer-supported instant messaging services (IMS) approaches have significant potential for diabetes management because support can be provided easily and prompt, is inexpensive, and needs less effort to attend compared to standard therapy. The major objective of the study is to analyze the impact of a peer-supported IMS intervention in addition to a standard diabetes therapy on the glycemic control of type 2 diabetic patients.

**Methods:**

A total of 205 participants with type 2 diabetes mellitus will be included and randomly assigned to an intervention or control group. Both groups will receive standard therapy, but the intervention group will participate in the peer-supported IMS intervention, additionally. The duration of the intervention will last for 7 months, followed by a follow-up of 7 months. Biochemical, behavioral, and psychosocial parameters will be measured before, in the middle, and after the intervention as well as after the follow-up.

**Discussion:**

Type 2 diabetes mellitus and other non-communicable diseases put healthcare systems worldwide to the test. Peer-supported IMS interventions in addition to standard therapy might be part of new and cost-effective approaches to support patients independent from time and place.

**Trial registration:**

ClinicalTrials.govNCT04797429. Registered on 15 March 2021.

## Administrative information

Note: the numbers in curly brackets in this protocol refer to SPIRIT checklist item numbers. The order of the items has been modified to group similar items (see http://www.equator-network.org/reporting-guidelines/spirit-2013-statement-defining-standard-protocol-items-for-clinical-trials/).

## Introduction

### Background and rationale {6a}

Diabetes mellitus is one of the four priority non-communicable diseases worldwide [1]. Globally, 463 million adults suffered from diabetes mellitus (9.3%) in 2019 and an increase of 51% of the prevalence is anticipated by 2045. Fifty-nine million adults are affected at the European level (8.9%) [2], while Austria shows a similar pattern: estimates range from 515,000 to 809,000 Austrians (7–11% of all inhabitants) suffering from diabetes [3]. In type 2 diabetes mellitus, which is the most common type of diabetes, hyperglycemia is the result of an inadequate production of insulin and insulin resistance, which means that the body cannot fully respond to insulin [2]. Type 2 diabetes mellitus is most commonly observed in adults over the age of 40 [4].

Diabetes can lead to serious long-term complications such as cardiovascular diseases, blindness, or the amputation of lower extremities as well as lower quality of life, poorer mental health like greater levels of depression, and reduced life expectancy [2]. Diabetes produces significant direct and indirect costs: 1.31 trillion USD in 2015 worldwide [5], 327 billion USD in 2017 in the USA [6], or 1.94 billion EUR even in Austria in 2014 [3].

Due to the chronic nature of diabetes, the disease requires continuous therapy, regular medical check-ups and good therapy adherence. Patient self-management behaviors in particular play an important role in the therapy of the disease: while healthcare professionals are responsible for only 5% of diabetes therapy, 95% are in the hands of the patients themselves, including, e.g., eating habits, physical activity, medication adherence, stress control, and disease monitoring [7]. Therefore, diabetes self-management education (DSME) (and support DSMES) play(s) a significant role in increasing a patient’s self-management capacity and improving diabetes therapy [8–11]. Self-management refers to the patient’s ability to manage symptoms, therapy, physical and psychosocial consequences, and lifestyle changes associated with living with a disease [12]. Consequently, DSME(S) is the process of facilitating skill, knowledge and abilities in diabetes self-care [11].

On the one hand, DSMES has been shown to improve clinical disease parameters like glycated hemoglobin (HbA_1c_) [13–15], which reflects the average plasma glucose level over the previous 8–12 weeks and is the preferred test for diabetes control [16], and even mortality [17]. On the other hand, research indicates that these outcomes might be difficult to maintain [18, 19] and seem to decline 1 to 3 months after the end of DSME(S) [20]. Consequently, effective strategies to preserve the effects of DSME(S) are needed.

Social support, defined as “an exchange of resources between at least two persons aimed at increasing the wellbeing of the receiver” [21], is a well-known predictor of diabetes self-management, improves self-efficacy, adherence and glycemic control [22, 23], and reduces healthcare costs [24]. Social support can be provided by several stakeholders like healthcare professionals, family members, friends or others living with the same disease (e.g., peers) [22].

Preliminary results show that peer support, which means support from a person who has experiential knowledge of a specific behavior or stressor and similar characteristics as the target population [25], is associated with better outcomes in terms of HbA_1c_, cardiovascular disease risk factors and self-efficacy [26–28] at lower cost [26] compared to standard therapy. Although those results are promising, research on peer support in diabetes care is still in its infancy [29, 30].

Peer support can be provided in various ways: face to face, telephone-based, web-based [29], or via other new technologies. New technologies in particular provide ideal and innovative means for peer support in diabetes management. Mobile Health (mHealth), which belongs to the group of information and communication technologies for health [31], supports medical practice using mobile devices such as mobile phones, monitoring devices, personal digital assistants, and other wireless devices [31]. Indeed, mobile phones have significant potential to serve as universal devices for diabetes management [32]. However, methodologically sound evaluation studies assessing the impact of mHealth are scarce [33, 34] and data security and other ethical concerns are often not sufficiently considered [32, 33]. Furthermore, most of the research on mHealth for diabetes focuses on support via apps or social media mainly provided by health professionals [34–37]. When it comes to support from peers or support provided via instant messenger services (IMS), less research is available. This is surprising because peer support IMS has particular advantages compared to other mHealth solutions:
In 2020, the majority (72.9%) of Austrians aged 45–64 who were mostly affected by the onset of type 2 diabetes mellitus used IMS, while only 27.5% used other social media tools [38].Off-the-shelf IMS technology is available which safeguards personal data protection, privacy and the associated ethical principles (e.g., *mattermost*: https://mattermost.com/).Compared to standard therapy, long-term support via IMS can be provided easily [26] and promptly [37], is inexpensive [26], and requires less effort to attend [39].

Generally, there is a need for high-quality randomized controlled trials (RCTs) on the impact of IMS telemedicine on health [40]. Moreover, personal influences like genetic factors have not been properly considered yet: most existing studies focus mainly on average therapy effects, even though personalized medical approaches show that the response to therapy varies significantly between diabetic individuals [41, 42]. In addition, theories from social sciences and psychology suggest that, depending on individual differences such as the regulatory mode, some individuals benefit more from mHealth interventions than others [29, 43, 44]. Furthermore, IMS users differ in terms of extraversion, neuroticism or conscientiousness [45], which might induce different health benefits related to personality traits.

The DiabPeerS study aims to implement a peer-supported IMS intervention for patients with type 2 diabetes mellitus and to analyze the effects of the intervention on type 2 diabetes mellitus-related outcomes-especially HbA_1c_. Furthermore, DiabPeerS aims to gain further insight into the associations of personal influences on the individual use, acceptance and effects of peer-supported IMS interventions in diabetes therapy.

### Objectives {7}

The major objective of the study is to analyze the impact of a peer-supported IMS in addition to an antidiabetic therapy according to current Austrian guidelines [4] (hereafter referred to as “standard therapy”) on the glycemic control of type 2 diabetic patients. We hypothesize that peer-supported IMS improves maintenance of diabetes self-management and, hence, leads to longer-lasting improved disease-specific outcome parameters (HbA_1c_) and higher quality of life. In particular, our main hypotheses are:

H1: A peer-supported IMS intervention reduces HbA_1c_ of patients with type 2 diabetes mellitus compared to a standard therapy.

H2: A peer-supported IMS intervention helps to maintain diabetes self-management behaviors in patients with type 2 diabetes mellitus compared to a standard therapy.

H3: A peer-supported IMS intervention improves the quality of life of patients with type 2 diabetes mellitus compared to a standard therapy.

H4: A peer-supported IMS intervention improves medication adherence in patients with type 2 diabetes mellitus compared to standard therapy.

Furthermore, we want to assess the correlation between the specific personality trait of extraversion and the benefits of peer-supported IMS.

H5: Extraversion correlates positively with the benefits of peer-supported IMS intervention as measured by the frequency of IMS usage, quality of life, and HbA_1c_ levels.

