The IMS strategy combines two aspects that are essential for IMS diabetes self-management peer support: 1. a communication strategy that takes into account the special requirement of IMS communication, i.e., approaches to raise engagement and activities in the group, and 2. a diabetes self-management support strategy to make sure that all topics which are known to be of importance for diabetes self-management [49] are covered and shared in a way that enables and empowers participants in their disease management. Thus, the IMS communication strategy contains, on the one hand**,** the IMS strategy which also involves a communication strategy that considers the special requirements of IMS and peer-communication on how to react and act in certain situations, for example, to achieve engagement. On the other hand, it entails a didactic plan which outlines how, in what form and how frequently diabetic content shall be shared with the participants by moderators (e.g., web links, exchange of personal experiences/opinions). This IMS strategy will be operationalized in form of the training curriculum.

The moderator and the way she or he communicates with the group plays a vital role in guiding the group, setting the tone and creating an atmosphere of trust and providing support. By introducing the moderators to certain communication strategies that are also displayed in detail in the guidebook and can be reflected upon in the monthly meeting with the dietitian, a trusting atmosphere in the IMS group should be facilitated.

After the intervention, a 7 month follow-up will be conducted. During the follow-up, the intervention group may use the IMS tool in a self-organized manner, i.e., without guidance by the dietitian, and continue to receive their standard therapy.

Participants who are assigned to the control group will continue to receive their standard therapy but will not be assigned to a *mattermost* group.

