Fasting blood glucose [mg/dl] as measured using Cobas 8000 (Roche Austria GmbH)Total cholesterol [mg/dl] as measured using Cobas 8000 (Roche Austria GmbH)High-density lipoprotein (HDL) [mg/dl] as measured using Cobas 8000 (Roche Austria GmbH)Low-density lipoprotein (LDL) [mg/dl] and triglycerides [mg/dl] as measured using Cobas 8000 (Roche Austria GmbH)Blood pressure [mmHg] as measured using Boso Medicus uno OABody height [cm], body weight [kg] and body fat [%] as measured using Seca mBCA 555. The device measures body weight with a scale, body height with ultrasound length measurement and body composition by the voltage drop of the alternating current in one step.Waist circumference [cm] to calculate the waist-to-height ratio as measured using an ergonomic, step less, and extendible measuring tape

Additionally, demographic data and personality traits will be surveyed in the baseline assessment (T0). Demographic data include age, gender, education, living arrangement (marital status), income, employment status, immigration background [63], and clinical information (age at diagnosis, on insulin, other medical therapies, list of prescribed medications). Personal traits will be assessed using the Big Five Inventory German (BFI-2) [64]. The BFI-2 captures “extraversion,” “agreeableness,” “conscientiousness,” “negative emotionality,” and “openness,” each represented by three sub-facets. The BFI-2 consists of 60 items using a five-item Likert scale with the endpoints “1” (strongly disagree) to “5” (strongly agree).

Additionally, participation in the disease management program “Therapie aktiv – Diabetes im Griff” as well as pregnancy and illicit drug use / non-medical use of prescription drugs will be evaluated at each measurement.

Communication data (real-time):

As part of the data export solution of the IMS communication data, an export script is provided in which individual rooms - these correspond to the groups assigned for the experiment - are listed. Such communication protocols containing the communication data of the individual groups can be retrieved on a daily basis. These data include, for example, the persons who have sent a post, sent texts and files, timestamps, or quotes. This information will be used to quantify the IMS communication activities.

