The posts will be evaluated by content analysis to explain and interpret the results of (H2) diabetes self-management behaviors, (H3) quality of life of participants, and (H4) medication adherence of participants. The codebook will be developed in collaboration with medical professionals for the coding of adherence and non-adherence behaviors. The quantified data will then be made available for the in-depth analysis of questionnaire data and medical scores.

According to past research [65–67], personality traits such as extraversion can influence our communication behavior: extraverted individuals speak more often, make more eye contact, smile, and nod more frequently than introverted persons. (H5) Therefore, we assume that extraversion will correlate positively with the number of posts as well as the number of reactions and emojis to posts from others.

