### Methods for additional analyses (e.g., subgroup analyses) {20b}

As we want to assess the association between specific personality traits and the benefits of peer-supported IMS, we use validated and published questionnaires, which we repeatedly distribute to all experimental and control groups at different times of the study.

In addition to the observed communication behavior, we use the information from the questionnaires (see {12}) to test the hypotheses and in particular related to (H2) diabetes self-management behaviors, (H3) quality of life of participants, and (H4) medication adherence as well as (H5) the level of extraversion.

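### H5 expresses differential benefit as a correlation of extraversion with quality of life and HbA1c levels, with no comparison with standard therapy, so as worded it cannot separate prognosis from effect modification

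*Protocol article*

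**What the plan says.** Under Objectives {7}, the Protocol article introduces its personality question with "we want to assess the correlation between the specific personality trait of extraversion and the benefits of peer-supported IMS". H5 follows: "Extraversion correlates positively with the benefits of peer-supported IMS intervention as measured by the frequency of IMS usage, quality of life, and HbA_1c_ levels". By contrast H1, and likewise H2 to H4, carries its comparator in the sentence: "A peer-supported IMS intervention reduces HbA_1c_ of patients with type 2 diabetes mellitus compared to a standard therapy".

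Three other sections bear on H5:

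- Outcomes {12} works out only the usage part: "we assume that extraversion will correlate positively with the number of posts as well as the number of reactions and emojis to posts from others". It also schedules the personality inventory for the baseline visit (T0).
- Methods for additional analyses {20b} restates the aim as "we want to assess the association between specific personality traits and the benefits of peer-supported IMS" and refers to questionnaires "which we repeatedly distribute to all experimental and control groups at different times of the study". It lists extraversion (H5) among the hypotheses to be tested with this information.
- Statistical methods {20a} names repeated measures ANCOVA for comparing the two arms and mentions no moderator term.

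The Background and rationale {6a} motivates the question as one of differential response: treatment response differs between patients, and some people gain more than others from mobile-health interventions.

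**The concern.** The background asks who benefits more. That is a question about how the difference between the arms changes with extraversion. H5 instead names a correlation of extraversion with outcome levels. Such a correlation also arises when extraverts report better quality of life whatever their treatment, so it mixes prognosis with effect modification. At stake is a published claim that extraverted patients gain more from peer messaging when the same association would be present under standard therapy.

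There is a second, smaller difficulty. One word for a positive correlation covers quality of life, where higher is better, and HbA1c, where H1 makes lower better. A reader cannot tell from H5 alone which sign for HbA1c would support it.

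**Working it through.** The plan gives no figure for H5; its sample size concerns the primary HbA1c comparison only. That size serves here as an input.

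**Inputs**
- From Sample size {14}: 98 per arm, 196 in total, 30% dropout, 5% significance level, f = 0.229.
- Completers: 98 × 0.7 = 68.6, so 68 or 69 per arm; 196 × 0.7 = 137.2, so 137 in total.
- Assumed, because the documents are silent: a correlation ρ of 0.1 to 0.3 between extraversion and the outcome level, equal in both arms; no effect modification; two-sided tests.

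**Step 1. One-arm correlation with the outcome level, unadjusted.** By Fisher's z, the expected test statistic is atanh(ρ) × √(n − 3). With n = 69, √66 = 8.124.

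| ρ | atanh(ρ) × 8.124 | Chance of p < 0.05 |
|---|---|---|
| 0.1 | 0.1003 × 8.124 = 0.82 | 0.13 |
| 0.2 | 0.2027 × 8.124 = 1.65 | 0.38 |
| 0.3 | 0.3095 × 8.124 = 2.51 | 0.71 |

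A simulation (4,000 runs per setting, constant treatment effect of 2 × 0.229 = 0.458 SD) counted significant positive correlations. It gave 13%, 37% and 72% with 68 per arm, and 16%, 52% and 86% with all 98. The control arm showed the same correlation about as often (52% at ρ = 0.2 with 98), so finding it in the intervention arm says nothing about benefit.

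**Step 2. The interaction test.** In the same simulated trials, the arm-by-extraversion term in a two-arm linear model was significant in 4.5% to 5.7% of runs across all settings.

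**Step 3. Milder readings of H5, still in one arm.**
- Change from baseline: if extraversion has the same covariance with the outcome at both visits, it cancels in the difference and the rate returns to about 5%.
- Baseline adjustment, with an assumed correlation of 0.6 between baseline and follow-up: the partial correlation is ρ(1 − 0.6) / √[(1 − ρ²)(1 − 0.36)]. For ρ = 0.2 this is 0.08 / 0.784 = 0.10; for ρ = 0.3 it is 0.12 / 0.763 = 0.16. With √(69 − 4) = 8.06, the rejection rates are about 13% and 25%.

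**Step 4. HbA1c direction.** Suppose extraverts truly gain more, by 0.3 SD of HbA1c per SD of extraversion. In simulation the correlation with the HbA1c level was then significantly negative in 81% of runs (n = 98) or 67% (n = 68), and significantly positive in none. The direction therefore has to be written down.

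**Step 5. What the interaction can detect.** With unit SDs and 1:1 allocation its standard error is 2/√N. At 80% power the detectable value is (1.96 + 0.84) × 2/√N:
- N = 196: 5.6 / 14 = 0.40.
- N = 137: 5.6 / 11.70 = 0.48.

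This is about the size of the 0.458 SD main effect that the trial was planned around.

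**The case against.** The strongest reply is that no section commits the trial to a one-arm correlation on raw levels. The article condenses a fuller protocol, and the exact model is commonly left to an analysis plan that is not shown. Methods for additional analyses {20b} gives the questionnaires to both arms and links them to H5, which points towards using both. All of this stands against calling the model missing. It does not remove the point, which concerns the hypothesis as published: an analysis that follows H5 literally inherits the problem, and one that tests an interaction departs from its wording.

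Four stronger readings are tempting, and the documents do not support them:

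- **That H5 has the wrong sign for HbA1c.** The thing said to correlate positively is the benefit, not the HbA1c value. Read with H1, H5 can mean a larger fall in extraverts. The fault is ambiguity.
- **That the control arm is left out.** No section restricts the quality-of-life or HbA1c part to the intervention arm.
- **That all of H5 is unsound.** Messaging use exists only in the intervention arm: "Participants who are assigned to the control group will continue to receive their standard therapy but will not be assigned to a" messaging group. A within-arm correlation is the right analysis there.
- **That false confirmation in 38% to 71% of trials is a property of the plan.** Those figures need an unadjusted one-arm level analysis and an assumed ρ of 0.2 to 0.3. At 0.1 the figure is 13%, and step 3 of the working shows lower rates under milder readings.

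It is also fair that H5 is set apart from the main hypotheses and that no section plans to offer the intervention by personality. The consequence is a misleading secondary claim, not a wrong primary result.

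**Conclusion.** The point holds for the quality-of-life and HbA1c parts of H5. As worded, they equate benefit with an outcome level and name no contrast with standard therapy, so H5 could be supported when extraversion does not modify the treatment effect at all.

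The size depends on assumptions that the documents do not settle. It is roughly 13% to 71% for an unadjusted one-arm level correlation with ρ between 0.1 and 0.3 and 68 or 69 completers. It is less with baseline adjustment, and about 5% with change scores if the trait's association with the outcome is stable. The interaction test stays near 5% without relying on these choices. The HbA1c direction is undefined rather than wrong. The primary analysis is unaffected. The change should still be made, because the data needed are already collected in both arms.

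**What to change.** For quality of life and HbA1c:

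- Reword H5 as effect modification: the difference between intervention and control, at a named visit, changes with baseline extraversion.
- Add extraversion measured at T0 and its product with arm to the baseline-adjusted model fitted to both arms.
- Report the interaction per SD of extraversion with its confidence interval.
- State the expected HbA1c direction: a larger reduction with higher extraversion.
- Label the analysis exploratory.

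Keep the simple within-arm correlation for messaging use only, and present it as a separate association with engagement.

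The cost is two model terms and a reworded sentence, with no new data. The drawback is limited power: only interactions of about 0.40 SD per SD of extraversion (196 analysed) to 0.48 (137 analysed) are detectable at 80%. A non-significant result should therefore be read from the interval and not as evidence of no modification.
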